**Missing data for outcomes**

For outcomes that are measured at multiple time points during follow-up, we have based our analysis strategy on that proposed by White et al 2011[7]. To deal with incomplete data (i.e. when patients have missing data at one of the follow-up time points) we will:

1. Attempt to follow up all randomised patients even if they withdraw from the study
2. Perform a main analysis of all observed data that are valid under a plausible assumption about the missing data
3. Perform sensitivity analyses to explore the effect of departures from the assumptions made in the main analysis
4. Account for all randomised participants, at least in the sensitivity analyses

We will therefore (a) include all patients with at least one post-randomisation assessment (i.e. if they have recorded data for at least one follow-up time point) in the analysis; (b) use mixed-effects models adjusted for baseline covariates, which assumes that the data are missing-at-random (i.e. they are missing based on their observed outcome at other time-points, and other patient characteristics); and (c) perform sensitivity analyses under other missing data assumptions (e.g. that patients who were lost-to-follow-up gained more weight than patients who remained in the trial).

**Analysis of primary outcome**

The primary outcome (change in weight at 12 months post-randomisation) will be analysed using a mixed-effects linear regression model. The model will include change in weight at 1, 2, 6 and 12 months as outcomes.

The model will include a random intercept for ‘cluster’ (group or nurse, depending on treatment arm). The correlation between observations at different time points from the same patient (1, 2, 6, and 12 months) will be modelled using an unstructured correlation structure. The model will be estimated using restricted maximum likelihood (REML). Treatment arm, time point (month 1, 2, 6, or 12), and the interaction between treatment arm and time point will be included in the model as fixed factors. Time point will be included as an indicator variable. The covariates listed in section 5 will also be included in the model as fixed factors.

The analysis will be implemented in Stata as follows:

mixed outcome treatment##time covariates || cluster_id:, || ///

patient_id:, noconstant residuals(unstructured, t(time)) stddev reml dfmethod(kroger)

If this model fails to converge, we will run the model again using the correlation structure

*residuals(ar 2 , t(time))*. If the model still fails to converge, we will use *residuals(ar 1 , t(time))*.

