**Table 5 – ICC values for group or nurse at 6 and 12 months**

|  | 6 months | 12 months |
| --- | --- | --- |
| Change in weight |  |  |
| Change in BMI |  |  |
| Change in waist circumference |  |  |
| Change in systolic blood pressure |  |  |
| Change in diastolic blood pressure |  |  |
| Food Craving Inventory score |  |  |
| Frequency domain |  |  |
| Strength domain |  |  |
| Food Knowledge Assessment Questionnaire score |  |  |
| Three Factor Eating Questionnaire score |  |  |
| Cognitive Restraint domain |  |  |
| Uncontrolled Eating domain |  |  |
| Emotional Eating domain |  |  |
| International Physical Activity Questionnaire |  |  |
| MET-minutes/week domain |  |  |
| Sitting domain |  |  |
| Participants losing 5% of their body weight |  |  |
| Participants losing 10% of their body weight |  |  |

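### The AR fallbacks for the primary model impose one residual variance on all four visits, so a fallback's 12-month standard error is too small if weight-change variance grows; the main model's single cluster variance is a narrower, conditional weakness

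*SAP*

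**What the plan says.** The SAP section Analysis of primary outcome defines a joint model: "The model will include change in weight at 1, 2, 6 and 12 months as outcomes". Clustering enters once: "The model will include a random intercept for ‘cluster’ (group or nurse, depending on treatment arm"). The Stata code agrees. It begins "mixed outcome treatment##time covariates || cluster_id", with no cluster-by-time term, and continues "patient_id:, noconstant residuals(unstructured, t(time)) stddev reml dfmethod(kroger"). The patient-level residual variance may therefore differ by month, while the cluster variance is one number for all months.

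The fallback rule begins: "If this model fails to converge, we will run the model again using the correlation structure". The structure named is "residuals(ar 2 , t(time")), followed if needed by "residuals(ar 1 , t(time")). Both carry one residual variance for every month.

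General analysis principles states that the ICC is assumed equal between WAP groups and control nurses. It says nothing about constancy over months. Table 5 plans "ICC values for group or nurse at 6 and 12 months".

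**The concern.** The primary inference is at month 12. Change from baseline often becomes more variable as follow-up lengthens. A model that gives month 1 and month 12 the same variance then averages the two and understates the uncertainty at month 12.

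The unstructured main model avoids this at patient level, but the fallbacks bring it back. They would be used when the main model does not converge, with no further check on the 12-month standard error.

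The single cluster intercept raises a similar question at cluster level. The SAP treats clustering as material, because it enlarged the WAP arm for it. If the model allows too little for clustering at month 12, part of that protection is lost. In Table 5 the 6- and 12-month ICCs could differ only through the residual variance, so the table would not show whether clustering itself had changed.

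**Working it through.** **1. The plan's own figures (Sample size determination).** Inputs: difference 1.3 kg, SD 3, two-sided 5%, 90% power, 18 per group, ICC 0.05.
- n per arm = 2 × (1.960 + 1.282)² × 3² / 1.3² = 111.9, so 112.
- Design effect = 1 + (18 − 1) × 0.05 = 1.85; 111.9 × 1.85 = 207.04, so 208.
- With 108 and 216: SE = 3 × √(1/108 + 1.85/216) = 0.4005; 1.3/0.4005 − 1.960 = 1.286; power 90.1%.

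These figures reproduce. The SD of 3 and the ICC of 0.05 are single values; the SAP gives neither by month.

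**2. Assumptions added for the check (not in the SAP).** Twelve WAP groups of 18; 5 nurses with 22 patients each; retention 90/80/65/50% at months 1/2/6/12 (only the 50% is the SAP's); within-patient correlations 0.4 to 0.8; SDs by month as in the table below.

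**3. Hand check of the fallbacks.** With SDs 1.5/2/2.5/3 the variances are 2.25, 4, 6.25 and 9. Weighted by retention, the common variance is (0.9 × 2.25 + 0.8 × 4 + 0.65 × 6.25 + 0.5 × 9) / 2.85 = 13.79/2.85 = 4.84. Its square root is 2.20, which is 0.73 of the true 12-month SD of 3.

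**4. Full check.** For each working model the expected REML criterion was minimised under the assumed true covariance. The model-based SE of the 12-month treatment effect was then divided by its true (sandwich) SE to give a ratio r. Type I error = 2 × [1 − Φ(1.96 r)], a normal approximation without Kenward-Roger. Each cell shows r, with type I error in brackets where it was calculated.

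| SDs at months 1/2/6/12; cluster effect | Unstructured (main) | AR(2) | AR(1) |
|---|---|---|---|
| 3/3/3/3; constant | 1.00 | 1.01 | 1.06 |
| 1.5/2/2.5/3; cluster variance flat | 1.00 (5.0%) | 0.83 (10.4%) | 0.85 (9.6%) |
| 1.5/2/2.5/3; ICC 0.05 each month | 0.84 (9.9%) | 0.74 (14.4%) | 0.77 (13.3%) |
| 1/1.5/2.5/3; ICC 0.05 each month | 0.80 (11.5%) | about 0.68 (18%) | about 0.68 (18%) |
| 2.5/2.7/2.9/3; ICC 0.05 each month | 0.95 (6.1%) | 0.93 (7.0%) | 0.97 (5.8%) |
| 1.5/2/2.5/3; cluster variance fading from about 0.30 to 0.15 | 1.09 (3.2%) | 0.85 (9.7%) | 0.87 (8.9%) |

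A repeat of the calculation gave 0.85 and 0.82 for the main model in rows 3 and 4, 0.92 to 0.94 in row 5, and about 0.84 for AR(1) in row 2.

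**5. Why row 3 fails in the main model.** The true cluster variance is 0.05 × 1.5² = 0.1125 at month 1 and 0.05 × 3² = 0.45 at month 12. The fitted single value is 0.114, close to the month-1 value. With a fitted residual variance of 8.755, the implied 12-month ICC is 0.114/(0.114 + 8.755) = 0.013 instead of 0.05.

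**6. Sensitivity of row 3, main model.** ICC 0.01 to 0.10 gives r from 0.96 to 0.76; 2 to 10 nurses gives 0.76 to 0.89.

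**7. Simulation of row 3 (276 REML fits).** Main model: mean SE 0.472 against an empirical SD of 0.608. Rejection was 12.7% with z and 9.1% with an assumed t on 15 df. AR(1): 0.436 against 0.616; 16.7% and 14.1%. The Monte Carlo standard error is about 2 points (√(0.127 × 0.873/276) = 0.020). Kenward-Roger df were not computed; the t on 15 df is a stand-in.

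**8. Alternative fallback.** A patient random intercept with month-specific independent residuals gave r of about 0.98 when only patient-level variance grows.

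**The case against.** A reader might infer that the primary model itself understates the 12-month standard error whenever weight-change variance grows. The documents do not support this. Unstructured residuals absorb patient-level growth in full (ratio 1.00 in row 2). Only growth in cluster-level variance causes the shortfall, and fading cluster effects turn it into an excess (1.09). The SAP does not show which applies. Under Timing of data collection, controls have fortnightly sessions to week 8 and then only the 6- and 12-month visits, while WAP has monthly sessions, so the direction is open.

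The fallbacks apply only on non-convergence, so their error is conditional on that as well as on growing variance. The type I errors also leave out the planned Kenward-Roger correction. In the simulation a t on 15 df reduced the excess without removing it. All of this stands and limits the point.

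It might also be said that the complete-case analysis under Sensitivity analyses for primary outcome already gives a 12-month check. It is defined only by who is included. The SAP does not say that earlier visits are dropped, so it is not yet that check.

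Nor does Table 5 contradict the model: its ICCs can differ by month through the residual variance. They simply carry no separate information on the cluster variance.

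**Conclusion.** The point holds in two parts of unequal strength.

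**Fallbacks.** AR(2) and AR(1) give up the month-specific variances that the main model has. With SDs of 1.5/2/2.5/3 the 12-month standard error is about 15% too small (type I error about 10%) if only patient-level variance grows, and about 25% too small if cluster variance grows too. With mild growth the shortfall is 3 to 7% (ratios 0.97 and 0.93), and with flat SDs there is none.

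**Main model.** The single cluster variance makes the 12-month standard error too small only if cluster variance in kg grows: about 0.82 to 0.85 of the true value under moderate to steep SD growth at a constant ICC of 0.05. It is right if cluster variance is flat and may be too large if cluster effects fade.

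The month SDs, constancy of the ICC, retention before month 12, correlations and number of nurses are all assumptions. The sizes show what could happen and do not predict this trial's error rate.

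**What to change.** 1. Replace the two AR fallbacks with a structure that keeps month-specific residual variances and all four visits, for example a patient random intercept with `residuals(independent, by(time))`. It has five patient-level variance parameters (one intercept, four residual), against two for AR(1), three for AR(2) and ten for unstructured. It keeps the single cluster intercept, so it does not cure the second part of the point.

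2. State that the 12-month complete-case sensitivity analysis uses 12-month data only, with the cluster random intercept and Kenward-Roger. It then serves as a check on the 12-month standard error and as the source of the 12-month ICC in Table 5.

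Two tempting alternatives should be avoided. Independent cluster effects for each month treat a group's effects at different months as unrelated. Where the SAP's model is exactly right, that gave ratios of 0.81 to 0.88 in one calculation and 0.91 to 0.94 in another. Dropping month 1 from a fallback conflicts with Analysis of secondary outcomes, which takes the 1-month effect from the same model.

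The cost is SAP wording and code, a few more variance parameters in a fallback, and a slightly wider confidence interval in the cross-check. The primary model does not change.

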**Changes from planned analysis in the protocol**

In the original trial protocol we specified we would use a baseline-observation-carried-forward approach (BOCF) for dealing with patients with missing weight data during follow-up. This approach assumes that all those who were lost to follow-up returned to their exact baseline weight. Whilst this approach has been commonly used in other randomised controlled trials, it is problematic because it will provide biased estimates of the treatment effect when this assumption is incorrect (i.e. when participants do not return to their exact baseline weight when they fail to show up to their 6 or 12 month appointment). In addition, BOCF will often lead to an inflated type I error (false-positive) rate as it tends to underestimate the standard error for the treatment effect (due to ignoring the within-patient variability in weight when imputing using BOCF).

We have therefore decided to use a mixed-effects linear regression model for the primary analysis. This analysis method provides unbiased estimates of treatment effect and correct type I error rates provided the data is missing-at-random (MAR); that is, that the probability that a participant is lost to follow-up depends on either their previous weight measurements (e.g. their weight at baseline and 6 months if they are lost-to-follow-up at 12 months), and baseline patient characteristics (See section 5 for variables we are adjusting for). [2]

This strategy of analysis has been widely recommended in the presence of missing outcome data. We made the decision to change analysis methods before we had any access to the trial data, or ongoing trial results, and therefore there is no risk of bias associated with this decision.

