**General analysis principles**

The main analysis for each outcome will use intention-to-treat (ITT) principles, meaning that all participants with a recorded outcome will be included in the analysis, and will be analysed according to the treatment group to which they were randomised. More information on which participants will be included in each analysis is available in the section below. All p-values will be two sided, and the significance level is set at 5%.

Analyses for all outcomes will be presented as:

- The number of participants included in the analysis, by treatment group;
- A summary measure of the outcome, by treatment group (e.g. mean (SD) for continuous outcomes, number (%) for binary outcomes);
- A treatment effect, with a 95% confidence interval;
- A two-sided p-value.

All analyses will account for clustering by group in the intervention arm, and clustering by nurse in the control arm. Each patient will be defined as belonging to a cluster, defined by which group they belonged to if they were in the intervention arm, and which nurse they were treated by if they were in the control arm. This variable will be included as a random intercept in a mixed-effects regression model. This analysis assumes the intraclass correlation coefficient is the same between groups in the intervention arm as it is between nurses in the control arm. The Kenward-Roger degree-of-freedom correction will be employed for all linear mixed-effects models.

All analyses will adjust for baseline weight, age, gender, ethnicity (White British, White other, Black, Asian, Mixed, or other), smoking status (smoker vs. non-smoker) and GP practice (Lawson vs. Barkantine) as covariates in a regression model. Outcomes which are measured at baseline will also be adjusted for the value of the outcome at baseline (this includes weight, BMI, waist circumference, systolic and diastolic blood pressure, Food Craving Inventory, Food Knowledge Assessment, Three Factor Eating Questionnaire, and IPAQ). Continuous covariates (baseline weight, age) will be assumed to have a linear association with outcome. Binary and categorical covariates (gender, ethnicity, smoking status, and GP practice) will be included in the regression model using indicator (dummy) variables. Missing baseline data will be accounted for using mean imputation.

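### Baseline weight has one slope for months 1 to 12 in the primary model, so the 12-month effect may be under-adjusted, and biased if dropout relates to baseline weight differently by arm

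*SAP*

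**What the plan says.** Under Analysis of primary outcome, the response is a four-visit vector: "The model will include change in weight at 1, 2, 6 and 12 months as outcomes". The within-patient correlation "will be modelled using an unstructured correlation structure". The fixed part is described as "Treatment arm, time point (month 1, 2, 6, or 12), and the interaction between treatment arm and time point will be included in the model", followed by "The covariates listed in section 5 will also be included in the model as fixed factors". The code has the same form, "mixed outcome treatment##time covariates", with no covariate-by-time term.

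The covariates come from General analysis principles: "All analyses will adjust for baseline weight, age, gender, ethnicity", then smoking status and GP practice. That section makes baseline weight linear in the outcome. It does not say whether its effect may change between visits.

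Under Changes from planned analysis in the protocol, the SAP drops baseline-observation-carried-forward. It argues that the mixed model is unbiased when loss to follow-up depends on earlier weights and on "baseline patient characteristics (See section 5 for variables we are adjusting for"). Sample size determination plans for half of each group to be unavailable at one year.

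**The concern.** The treatment effect is free to differ at each visit, but the adjustment for baseline weight is not. The 12-month comparison therefore receives whatever slope best fits all four visits together.

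A constant slope is doubtful for change in weight. The SAP's own background reports a mean loss of 2.8 kg at end of treatment and 4.5 kg at the 3-month follow-up in the pilots, and two secondary outcomes count loss as a percentage of body weight. If loss scales even partly with body weight, the slope moves as mean loss moves.

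Two things are at stake at the primary time point. One is precision. The other is the missing-data argument: missingness at random is not enough on its own, because the mean model must also be right at 12 months. With 50% loss planned, a good deal rests on that model.

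**Working it through.** **1. The plan's own figures.** Inputs from Sample size determination: difference 1.3 kg, SD 3 kg, two-sided 5%, power 90%, cluster size 18, ICC 0.05.

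- n per group = 2 × (1.960 + 1.282)² × 3² / 1.3² = 111.9, so 112, as stated.
- Design effect = 1 + 17 × 0.05 = 1.85, and 112 × 1.85 = 207.2, so 208, as stated.
- With the design effect in the intervention arm only, 110 and 220 give SE = 3 × √(1/110 + 1.85/220) = 0.397 and power of 90.6%.

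The sample size is sound. The 1.3 kg, the SD of 3 kg and the 50% loss carry forward.

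**2. Assumptions the SAP does not supply.**

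- SD of change 1.5, 2, 2.5 and 3 kg at months 1, 2, 6 and 12 (only the last is from the SAP), with between-visit correlations of 0.45 to 0.85.
- Heavier participants lose more. The correlation r of baseline weight with 12-month change is 0.1 to 0.4. At months 1, 2 and 6 it is 0.33, 0.45 and 0.75 times that.
- 220 and 110 participants, true effect -1.3 kg, half missing at 12 months.
- Cluster intercept and other covariates left out.

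**3. Where the shared slope lands.** With complete data the common slope is a weighted average of the visit slopes, with weights proportional to V⁻¹1, where V is the between-visit covariance. At r = 0.3 the visit slopes are 0.149, 0.270, 0.562 and 0.900 kg per SD of baseline weight (signs dropped), and the weights are 1.23, -0.33, 0.02 and 0.08. The shared slope is 1.23 × 0.149 - 0.33 × 0.270 + 0.02 × 0.562 + 0.08 × 0.900 = 0.18. So only 0.18 of the 0.90 kg per SD is adjusted for at month 12.

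**4. Precision.** With s the true 12-month slope (3r) and d the part left unadjusted, SE ratio = √[(9 - s² + d²) / (9 - s²)].

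| r | s | shared slope | d | SE ratio, formula | SE ratio, simulated (no dropout, or dropout unrelated to arm) |
|---|---|---|---|---|---|
| 0.1 | 0.30 | 0.056 | 0.244 | 1.003 | 1.003 |
| 0.2 | 0.60 | 0.115 | 0.485 | 1.014 | 1.011-1.014 |
| 0.3 | 0.90 | 0.180 | 0.720 | 1.031 | 1.026-1.032 |
| 0.4 | 1.20 | 0.258 | 0.942 | 1.057 | 1.052-1.060 |

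**5. Bias at 12 months (kg).** There were 300 simulated trials per scenario, with Monte Carlo error about 0.43/√300 = 0.025. Dropout changes by a log-odds of 1 per SD of baseline weight (odds ratio 2.7). Each cell gives the shared-slope result, then the result with baseline weight by time.

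| r | Same relation in both arms | One arm only | Opposite directions |
|---|---|---|---|
| 0.1 | +0.023 / +0.022 | +0.035 / -0.032 | +0.157 / +0.023 |
| 0.2 | -0.003 / -0.004 | +0.134 / -0.005 | +0.296 / +0.022 |
| 0.3 | +0.036 / +0.035 | +0.226 / +0.008 | +0.404 / +0.012 |
| 0.4 | +0.028 / +0.024 | +0.249 / -0.011 | +0.528 / -0.012 |

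The sign is positive because heavier participants were made to leave the WAP arm, which understates its benefit. Reversing the pattern reverses the sign.

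Hand check at r = 0.3, one arm: with p the dropout probability, those who stay have mean baseline weight -E[p(1 - p)]/0.5 = -0.2066/0.5 = -0.41 SD. The unadjusted slope gives 0.72 × 0.41 = 0.30 kg if earlier visits recover nothing. The simulated 0.23 kg is lower because they recover some. When the relation is the same in both arms, the shift is the same and cancels.

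**6. Separate simulations in kg per kg** (assumed baseline SD 15 kg).

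- Log-odds 0.45 per SD, month-12 slopes -0.03, -0.06 and -0.10. Same relation in both arms: -0.009, -0.013 and -0.017 kg. One arm only: 0.045, 0.116 and 0.205 kg in size, with 95.5%, 94.3% and 92.8% coverage.
- Opposite directions, log-odds ±0.4 or ±0.5, slopes growing to -0.06 and -0.10: 0.22 and 0.53 kg, with 92% and 78% coverage. The interaction model gave at most 0.02 kg and 94-95%.
- Slope truly constant: variance ratio of the two models 0.998.

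**The case against.** The strongest reply is that the problem is conditional throughout. The SAP gives no slope of weight change on baseline weight at any visit, so under-adjustment cannot be shown from it. If loss were simply proportional to weight, with a mean weight of about 95 kg (an assumption), the planned mean losses of 0.4 to 3 kg would imply slopes of only 0.4/95 to 3/95, about 0.004 to 0.03 kg per kg. At 0.03 the variance rises by 0.7% and the bias is 0.045 kg (one arm) or 0.096 kg (opposite directions), with coverage still 95%. That stands, and it is why the smaller figures deserve more weight than the larger ones.

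A reader might infer that any dropout related to baseline weight biases the result. It does not: the relation must differ between arms. The sample size section assumes the same follow-up in both. Against that, Timing of data collection gives the WAP arm monthly sessions from month 3 and the control arm only 6- and 12-month visits, so a differing relation is conceivable but not shown.

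A reader might also take 0.53 kg with 78% coverage, or a 21% higher variance, as the expected size. Both need a slope of 0.10 kg per kg, which is 1.5 kg per SD and a correlation near 0.5 with an SD of 3 kg. The bias figure also needs heavier people to leave one arm while lighter people leave the other. Nothing in the SAP points to that.

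The planned complete case analysis would estimate a 12-month slope if fitted to 12-month data alone. The SAP does not say how it is fitted, and it would not repair the primary estimate.

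**Conclusion.** The reading of the model is certain: one baseline-weight slope for all four visits, in text and code. The consequence is conditional on that slope changing over follow-up. If it does, the usual cost is a slightly larger standard error, and the planned test remains valid. Bias arises only if dropout relates to baseline weight differently by arm. It is then about 4-19% of the planned effect in the one-arm case (0.05/1.3 to 0.25/1.3) and up to about 38% (0.5/1.3) in an extreme case. So the SAP's statement that the model is unbiased when loss depends on baseline characteristics is not assured by the model as coded.

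The documents do not support a claim that the primary result will be biased, or that age, gender, ethnicity, smoking and practice need the same treatment. All slopes, the baseline SD, the visit SDs before month 12 and the dropout patterns are assumptions. This is a worthwhile low-cost improvement, not a flaw that invalidates the analysis.

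**What to change.** Add `c.baseline_weight##i.time` to the primary model and one sentence to Analysis of primary outcome saying that the baseline-weight effect may differ by time point. In the linear secondary models, interact the outcome's own baseline value with time point in the same way. Leave the other covariates as main effects. The alternative is to state and justify a constant slope.

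The cost in the primary model is 3 degrees of freedom. There was no measurable loss of precision when the slope was constant. Where dropout does run in opposite directions by arm, the reported standard error can be somewhat larger (0.459 against 0.437 at r = 0.1), because the model then accounts for the imbalance in baseline weight among those observed.

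The change should be made before unblinding, as the Kenward-Roger amendment was. If outcome data by arm have already been seen, report it as a labelled sensitivity analysis beside the planned model.
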